**Figure 2 F2:**
[figure not shown]
**Diagram of the hypothesised relationships between experimental variables.** This figure illustrates direct **(A)** and meditational **(B** and **C)** relationships between experimental (e.g. autonomous motivation) and dependant variables (e.g. implementation).

We will deal with missing data using full-information-maximum-likelihood estimation (FIML). Traditional approaches to missing data (*e*.*g*., list-wise or pair-wise deletion) can lead to considerable bias in parameter estimates. In contrast FIML provides a superior approach to dealing with missing data that uses all the available information for parameter estimation [54].

Standard multiple regression analysis will test for predictors of transfer. In terms of knowledge transfer related to the new workplace practices, we will compare current findings with the pre-post effect sizes extracted from the previous work conducted by the research team [51]. In that study, effect sizes were moderate based on Cohen’s criteria (STARS = 0.25, RKI = 0.52) with a sample size of 75. Given the additional components of this intervention we are expecting slightly higher effect sizes. Data collected in the CRM-VQ will enable comparison of these predictors with participant self-reported implementation of the new work practices.

Work-sampling audits will also be used as an objective measure of transfer. We are anticipating a sample size of 200 at time point one, but have allowed for a more modest sample size of 100 in calculating power analyses. In our previous study, we found 37% of people transferred training. With this information we are able to estimate the percentage of people who need to demonstrate transferred practices in work samples in order to show a significant increase in the proportions between the former and present studies. Using Z test for proportions we have calculated that we need at least 48 out of the 100 participants to obtain a significant difference at p<0.01 to detect a 10% increase in transfer. We believe this difference is very achievable with the addition of the values-focused interventions.

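### The 48-of-100 figure is the smallest significant count, not a power calculation: a true 10-point rise in transfer would reach it only about 46% of the time

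*Protocol article*

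**What the plan says.** The final paragraph of Methods, Data analysis, in the protocol article deals with the work-sampling audits. The authors expect 200 participants at the first time point but "have allowed for a more modest sample size of 100 in calculating power analyses". The reference rate comes from their own earlier work: "In our previous study, we found 37% of people transferred training". The aim is to find the percentage who must show transfer "in order to show a significant increase in the proportions between the former and present studies". The method and result follow: "Using Z test for proportions", they conclude that "we need at least 48 out of the 100 participants to obtain a significant difference at p<0.01 to detect a 10% increase in transfer". The paragraph ends: "We believe this difference is very achievable with the addition of the values-focused interventions".

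It gives no power or type II error. It does not say whether the test is one- or two-sided, whether 37% is treated as fixed or as an estimate, or whether 10% means percentage points or a relative increase.

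**The concern.** A significance cut-off and a detectable effect are different quantities. The cut-off is the result that must be observed for p to fall below alpha. The detectable effect is the true rate at which that result would be observed with a chosen high probability, and it must lie well above the cut-off. The paragraph computes the first and words it as the second, through the label of power analysis and the phrase "to detect a 10% increase in transfer".

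This is the only sample-size calculation with figures in the article. A reader would take from it that 100 participants give a good chance of finding a 10-point rise over the former study at the 1% level. If they do not, a non-significant comparison at that size says little about whether such a rise occurred.

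**Working it through.** **Inputs**, all from the last paragraph of Data analysis: reference rate p0 = 0.37; n = 100 (200 anticipated); alpha 0.01, sidedness not stated; a 10% rise, read first as 10 points, so p1 = 0.47. One further input is assumed where marked: 75 people behind the 37%. The article gives 75 as the former study's sample size for the knowledge and attitude measures, not expressly for the transfer rate.

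**Reproducing the plan's figure.** One-sample Z test with null variance:

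cut-off = n·p0 + z·√(n·p0·(1 − p0)), with √(100 × 0.37 × 0.63) = √23.31 = 4.828.

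- One-sided 0.01: 37 + 2.326 × 4.828 = 48.23, which rounds to the stated 48.
- Strictly, 48 gives z = 11/4.828 = 2.278 and one-sided p = 0.0114. The first count with p<0.01 is 49 (p = 0.0065).
- Two-sided 0.01: 37 + 2.576 × 4.828 = 49.44, so 50.

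The 48 is therefore a critical value, with no power term in it. It is an observed excess of 11 points, whereas a true rate of 47% gives an expected count of 47.

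**Power at n = 100**, exact binomial P(X ≥ cut-off), 37% fixed, workers independent:

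| True rate | Cut-off 48 (as stated) | Cut-off 49 (one-sided) | Cut-off 50 (two-sided) |
|---|---|---|---|
| 47% (10 points) | 45.9% | 38.1% | 30.8% |
| 48% (11 points) | 53.9% | 46.0% | 38.2% |
| 40.7% (relative 10%: 0.37 × 1.10) | 8.4% | 5.7% | 3.7% |

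**Detectable rate, one-sample form.** Normal approximation:

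power = Φ{[p1 − p0 − z·√(p0(1 − p0)/n)] / √(p1(1 − p1)/n)}.

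Setting power to 80%:

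- n = 100: p1 = 52.4% (one-sided 0.01) or 53.6% (two-sided).
- n = 200: p1 = 47.9% or 48.8%.

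The n for 80% power at 47% is [(z·√0.2331 + 0.842·√0.2491)/0.10]², which is 239 one-sided or 277 two-sided. Exact power at n = 200 and 47% is 73.8% (90 needed) or 63.8% (92 needed).

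**Two-sample form.** The paragraph describes a difference between two studies, so the 37% has its own sampling error. With 75 earlier participants (assumption) against 100:

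- pooled rate = (75 × 0.37 + 100 × 0.47)/175 = 0.427
- standard error under no difference = √(0.427 × 0.573 × (1/75 + 1/100)) = 0.0756
- standard error at 37% v 47% = √(0.2331/75 + 0.2491/100) = 0.0748
- one-sided power = Φ[(0.10 − 2.326 × 0.0756)/0.0748] = Φ(−1.01) = 15.6%
- two-sided power = Φ[(0.10 − 2.576 × 0.0756)/0.0748] = Φ(−1.26) = 10.3%

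On this form, 80% power needs a true rate of about 61% (one-sided) to 63% (two-sided) at n = 100, and about 58% to 60% at n = 200.

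**Clustering.** Correlation within worksites widens the spread of the count. With the cut-off held at 48 and an expected count of 47, a wider spread moves power towards one half but not above it. Where power is already above one half, a wider spread lowers it, so the rates needed for 80% power would rise.

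**The case against.** The strongest reply is that the paragraph largely says what it computes: the percentage needed for a significant result. It states no power, so no power figure is wrong, and 48 is recovered by rounding. All of that stands. The fault lies in the label and the detection wording, and it remains with 48 taken as correct.

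The closing belief that the difference is achievable may also refer to the 48-of-100 result, not to a true 47%. If the true rate is 48% and the cut-off stays at 48, power is 53.9%, so significance is slightly the more likely outcome. That stands too, but about 54% is still not what a power analysis is meant to secure.

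Three stronger readings might be inferred, and the article supports none of them.

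- That a non-significant comparison would be taken as failed transfer: the article does not say how such a result would be interpreted.
- That a fall from 200 to 100 is accepted on the strength of this paragraph: 100 is only a cautious figure used in the calculation. It is not set as a target or minimum, and the Discussion links the larger expected sample to staff turnover.
- That the trial's main comparison is underpowered: Data analysis places primary interest in cluster-level effects and compares values with implementation coaching through Models A to C. The Z test is a secondary comparison with the former study, and nothing here bears on the power of the randomised contrast.

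**Conclusion.** The point holds as a misdescribed calculation. The count of 48 is the minimum significant result for a one-sided one-sample test, and the claim to detect a 10-point rise does not follow from it. On the most favourable assumptions (37% known without error, independent workers, 48 accepted) power is about 46%. It is 38% or 31% at cut-offs that meet p<0.01 one-sided or two-sided. On those assumptions the rise detectable with 80% power at n = 100 is about 15 to 17 points, and even 200 participants fall short of 80% power for 10 points.

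Every other reading tried for a 10% increase (sampling error in the 37%, a stricter cut-off, a relative 10%) gives lower power. The two-sample figures rest on the assumed denominator of 75 and would change with the real one. The effect of clustering is given in direction only, because the article provides no intracluster correlation.

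**What to change.** Keep the sample and rewrite the paragraph:

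1. Describe the count as the minimum significant result, and state the test form and sidedness. It is 49 one-sided or 50 two-sided if 37% is treated as fixed.
2. Remove the words "to detect a 10% increase in transfer".
3. State the increase detectable at a named power, together with its conditions. For example: with 37% taken as fixed and workers independent, 80% power at alpha 0.01 needs a true rate of about 52 to 54% at n = 100 and about 48 to 49% at n = 200 (one-sided to two-sided). These figures should not be printed without those conditions.
4. Because the comparison is between two studies, add the two-sample figures using the former study's actual denominator for the 37%. If it were 75, power for a 10-point rise at n = 100 would be about 10 to 16%, and 80% power would need about 61 to 63% at n = 100 or 58 to 60% at n = 200.
5. Note that clustering by worksite raises these rates further.
6. Report the estimated difference from the former study with its confidence interval.

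The cost is the wording of one paragraph and a look-up of one denominator in the authors' own earlier data. No participants, measurements or procedures change, though the stated sensitivity becomes less favourable.

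### The planning figure for work-sample transfer is miscalculated: 48 of 100 against 37% does not reach p<0.01, and the step from 37% to 48% is 11 points, not 10

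*Protocol article*

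**What the plan says.** The calculation is in the last paragraph of Methods, Data analysis, in the protocol article. About 200 participants are expected at the first time point, but the authors "have allowed for a more modest sample size of 100 in calculating power analyses". The reference rate is given as a whole percentage: "In our previous study, we found 37% of people transferred training". The method named is a Z test for proportions, and the result is worded as follows: "we need at least 48 out of the 100 participants to obtain a significant difference at p<0.01 to detect a 10% increase in transfer". The paragraph presents this as showing how many people must transfer for the proportion to rise significantly from the former study to the present one, and calls the difference very achievable.

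It does not say whether the test is one-sample or two-sample or one-sided or two-sided, what the denominator of the 37% was, or what power is attached to the increase. The preceding paragraph gives effect sizes for two staff questionnaires from earlier work "with a sample size of 75", but does not tie that number to the 37%.

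**The concern.** All the inputs to a simple test are stated, and so is its result, so the result can be checked. It is offered as a completed calculation, not as something left to a later plan.

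Three things look wrong. The count does not deliver the stated significance level. The increase named in the sentence is not the one the count implies. And the number answers a different question from power: it says what would have to be observed, not how likely that is.

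It is the only numerical planning figure given for work-sample transfer, and the optimism about reaching it rests on it. A reader using it would think the comparison with the earlier study less demanding than it is.

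**Working it through.** **Inputs** (Methods, Data analysis): reference rate 0.37; n = 100; Z test for proportions; p<0.01; stated count 48. Sidedness is not stated, so both are shown. The earlier study's size is not stated for the 37%, so a range is used.

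**1. Trying to reproduce 48, with 37% fixed.**

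Standard error under the reference rate = √(0.37 × 0.63 / 100) = 0.0483.

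Critical count = 100 × (0.37 + z × 0.0483):
- one-sided 0.01, z = 2.326: 48.23, so 49 is the first count that passes;
- two-sided 0.01, z = 2.576: 49.44, so 50 is the first count that passes.

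The stated 48 looks like 48.23 rounded down, although a minimum count has to be rounded up.

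**2. The p-values at and around 48**, with z = (x/100 − 0.37) / 0.0483:

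| Count of 100 | z | p one-sided | p two-sided |
|---|---|---|---|
| 47 | 2.071 | 0.0192 | 0.0383 |
| 48 | 2.278 | 0.0114 | 0.0227 |
| 49 | 2.485 | 0.0065 | 0.0129 |
| 50 | 2.693 | 0.0035 | 0.0071 |

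Other forms of the one-sample test at 48 are no kinder. One-sided p is 0.0138 with the sample standard error, 0.0148 with a continuity correction, 0.0129 by arcsine, 0.0119 by logit, 0.0125 by likelihood ratio and 0.0158 by exact binomial.

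**3. The increase.** 48 − 37 = 11 points. A 10-point rise is 47 of 100, which misses p<0.01 by more (first row). A 10% relative rise would be 0.37 × 1.10 = 40.7%, further still from 48.

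**4. Allowing for sampling error in the 37%.** A comparison between two studies calls for the two-sample pooled Z test:

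z = (p₂ − p₁) / √[p̄(1 − p̄)(1/m + 1/100)], where m is the earlier study's size, p₁ and p₂ are the earlier and present proportions, and p̄ is the pooled proportion.

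Worked case, m = 75 (assumed). The only whole count out of 75 that rounds to 37% is 28 (27/75 = 36.0%, 28/75 = 37.3%). At 48 of 100, p̄ = 76/175 = 0.434, the difference is 0.1067 and the standard error is 0.0757. So z = 1.41 and two-sided p = 0.16.

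| Earlier study (assumed) | two-sided p at 48/100 | first count, one-sided p<0.01 | first count, two-sided p<0.01 |
|---|---|---|---|
| 28/75 | 0.159 | 56 | 57 (p = 0.00999) |
| 37/100 | 0.116 | 54 | 56 |
| 74/200 | 0.067 | 52 | 53 |
| 370/1000 | 0.031 | 49 | 51 |

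**5. Power.** If true transfer is 47%, the binomial chance with n = 100 is 0.46 of observing 48 or more, 0.38 of 49 or more and 0.31 of 50 or more.

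**The case against.** The strongest defence is that the miss is tiny on the most lenient reading. With a one-sample, one-sided test the critical value is 48.23, so the count is short by one participant. The 37% is also rounded: an unrounded rate between 36.5% and about 36.77% would make 48 pass one-sided (p = 0.0085 at 36.5%, 0.0098 at 36.75%). A planned increase is fairly read as one-sided. This stands as arithmetic, so it would be too strong to say that no conceivable version of the test yields 48. But the article states 37%, not a lower rate. Even at 36.5% the two-sided p is 0.017. And the defence requires an earlier study's result to be treated as known without error, which does not fit a comparison between two studies.

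Second, the larger gaps depend on a denominator that the article does not give. That is right. The 75 belongs to the questionnaire effect sizes, and Study design and procedure mentions two earlier projects. It is one assumed value in a range, and the cut-off of 57 should not be taken as established. The direction does not depend on it: 48 misses p<0.01 at every earlier size shown.

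Third, the 10 versus 11 mismatch may be loose wording, with 48 meant as the first count above a 10-point rise. That is possible, but the sentence ties the count to a significance level, which 47 does not reach and 48 does not either.

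Fourth, a reader might infer that 48 of 100 is the trial's success rule and would be reported as p<0.01. The article does not say so. It estimates what would be needed, and nothing suggests the test would not be computed on the actual data.

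Fifth, worksite clustering would widen the standard error. The article gives no intracluster correlation for this outcome, so no figure for it is claimed here.

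**Conclusion.** The point holds as an error in a stated planning figure. On the article's own inputs, 48 of 100 gives p = 0.011 one-sided or 0.023 two-sided, not p<0.01. The correct count is 49 or 50 if 37% is treated as fixed, a shortfall of one or two participants. If the 37% is treated as an estimate, as the described comparison implies, the two-sided cut-off is 53 to 57 for an assumed earlier size of 200 down to 75, a shortfall of five to nine. The stated 10% does not match the 11 points the figure uses. The calculation also supplies no power; at a true rate of 47%, the chance of reaching even 48 is slightly under one half, so the calculation does not support describing the difference as very achievable.

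This does not touch the main comparison. The figure concerns a historical comparison with an earlier study, whereas Data analysis places the primary interest in cluster-level effects and tests values against implementation within the trial. The sample of about 200 workers at 22 sites is not derived from this calculation. The results rest on 37% as printed, independent observations and, for the two-sample figures, the assumed earlier sizes.

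**What to change.** In Methods, Data analysis:

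- Restate the figure as a two-sample Z test using the earlier study's actual numerator and denominator, and state whether it is one-sided or two-sided. If the authors knowingly treat 37% as a fixed benchmark, say so and give 49 of 100 (one-sided) or 50 of 100 (two-sided).
- Say whether the increase is in percentage points or relative, and make it match the count.
- Give the power for that increase at n = 100, separately from the count needed for significance.
- Reword the statement about how achievable the difference is in the light of that power.

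This is a correction to one paragraph. It needs one number the authors already hold, the denominator of the 37%. The stated figure becomes less favourable; recruitment, randomisation and the between-condition analysis are unchanged.

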## Discussion

### Anticipated challenges

There are a number of challenges to carrying out this project due to the applied and organisational nature of this research. The schedule of intervention needs to meet standards of feasibility and pragmatism for the partner organisations, which are contributing significantly in terms of in-kind and cash contributions. Such challenges include the need to roll-out intervention components at a rate that enables partners (who are service providers) to equip and up-skill staff and accommodate the needs of new staff, which will at times put pressure on the capacity of the research team to deliver the intervention. Additionally, the need for interventions (particularly coaching) be practical and manageable has influenced the choice of methodology to be employed (*e*.*g*., GROW method to structure coaching interactions). A prime focus for the partner organisations and the research team has been ongoing sustainability of the interventions beyond the formal support of this project. This has necessitated the interventions be amenable to being ‘passed on’ to in-service champions in a train-the-trainer model, for example.

There is risk of data loss due to the multiple time points and staff turnover rates within the mental health field. Turnover of staff in mental health service organisations is up to 26% per annum [55]. These risks are being managed by allocation of a designated project coordinator within the research team, who will provide day-to-day liaison with the industry partners and take oversight of the intervention schedules and data collection. Each industry partner will identify a liaison officer who will have carriage of the coordination and scheduling responsibilities within their organisation. Our relatively large sample size anticipated for time pointone has been estimated with consideration given to the aforementioned industry attrition rate.

A further challenge in this research is to maximise fidelity to condition in this project. As stated above, cluster randomisation by worksite was adopted as a primary means of reducing contamination and enhancing utility and effectiveness of the rollout within the workplace. It is not possible to blind staff to condition, and it is likely there will be a degree of contamination as staff discuss the changes to work practice with colleagues from other sites (*e*.*g*., at training days or meetings). Participants in each condition will be aware that their colleagues may be receiving different components of training in the other condition. To address commitment to condition, both groups receive a strong rationale for the training and coaching approach they receive. Consistency to condition will be monitored specifically via the coaching record form completed alongside monthly coaching sessions. A ‘lessons learned’ and ‘risk register’ will be kept to manage these challenges, and are important to the ongoing development of the implementation literature.

## Conclusion

Training continues to be a popular method used in workforce development, yet the problem of inadequate transfer continues [56]. With reported annual training investments exceeding $50 billion in large economies like the United States [57], even modest increases in the return on investment is highly desirable. This research has wider significance to all workforces in terms of understanding the factors that influence and promote uptake of organisational change initiatives. To our knowledge, there are no other research studies in the organisational context that employ specific values-based protocol as a means to enhancing worker autonomy for and uptake of desired practices. Indeed, in the area of mental health, ‘effective transfer’ has benefits, including optimal provision of services to those within a vulnerable population, that may be argued as more important than the significant fiscal advantages outlined above. A key priority of many recent policy statements of governments across Europe and English-speaking economies is delivery of recovery-oriented service [58,59]. This research aims to directly address this priority area. While not elaborated here, we foresee cumulative benefits to mental health service participants, staff, and organisations as a result of the impacts of this specific intervention on employee satisfaction and wellbeing. These results have been demonstrated in previous studies investigating self-concordance of goals [27,28].

While problems of implementation are being acknowledged more widely, there is still uncertainty as to how to operationalise and measure successful transfer [60,61]. In particular, the role of values as a means to promoting uptake and a construct to be measured within the science of implementation requires elaboration. A range of models and measures exist to explain and capture uptake of new practices, ranging from attitudinal [62] to supervisor-rated [63], objective measures of observed performance on the job [64], and composite measures that combine multiple elements [65]. While the latter of these allow a snapshot of whether a desired practice is being carried out within the workplace, they do not allow us to make any assertions about ‘how’ the work is being done.

Our study explores the relevance of values in promoting ‘role-extra’ behaviours that represent enactment of embedded principles within implementation initiatives. The relevance of working from a values base and enabling staff involved in a change-initiative to connect with the principles embedded within it, is emphasised in the field of mental health recovery [66]. The important and little-explored issue of measuring adherence to the values in which a desired practice is embedded will be investigated further in this research.
